### Data safety monitoring committee

A DSMC has been established and has met prior to commencing this study. *A priori* stopping rules include:

#### Efficacy

A Fleming-Harrington-O’Brien [44] stopping boundary will be used at the interim analysis (described below), with a nominal *P*-value required for significance of .001. The final analysis will be referred to a nominal significance level of .0497. An interim analysis of the primary endpoint will be conducted after the first 126 subjects have completed the 12-month follow-up post the second vaccine dose. Sixty-three subjects per group will provide 80% power (α = 0.05, two-sided) to detect a reduction in exacerbations of 30%. At this point, and in discussion with the DSMC, a decision will be made with respect to continuing recruitment based on both the statistical significance and clinical relevance of any effect observed.

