### Sample size

Prospective data collected in Brisbane children with non-CF bronchiectasis indicate a mean annual incidence of 2.1 (standard deviation 1.046) exacerbations requiring hospital clinic attendance or hospitalisation. PHiD-CV efficacy against exacerbations in children with bronchiectasis is unknown. However, based on the aforementioned pilot data and AOM data from the POET study (30% reduction) [33], our trial is powered to detect a 30% reduction from 2.1 to 1.47 exacerbations in the 12 months following the second vaccine dose. Assuming a Poisson distribution, 93 children per group will provide 90% power (α = 0.05, two-sided) to detect a 30% reduction in exacerbations in the PHiD-CV group and 80% power to detect a 25% reduction. Assuming a 10% loss to follow-up, we will recruit 206 children (103 per group). Differences of less than 20% are unlikely to change clinical practice without additional supporting evidence.

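### The interim look is described by 80% power at α = 0.05, but its only efficacy boundary is P = .001, where 63 per group have about 26% power for the design effect

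*Protocol article*

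**What the plan says.** The Sample size section takes "a mean annual incidence of 2.1 (standard deviation 1.046) exacerbations requiring hospital clinic attendance or hospitalisation" as the control rate and says that "our trial is powered to detect a 30% reduction from 2.1 to 1.47 exacerbations in the 12 months following the second vaccine dose". Its power statements are "Assuming a Poisson distribution, 93 children per group will provide 90% power (α = 0.05, two-sided" for that effect, and "80% power to detect a 25% reduction" with the same number.

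The Efficacy subsection under the data safety monitoring committee (DSMC) places one interim analysis after 126 children have completed the 12 months following dose 2. The nominal P-value at that look is the one "required for significance of .001"; the final level is .0497. The number at the look is then justified by the statement that "Sixty-three subjects per group will provide 80% power", for a 30% reduction and with a two-sided α of 0.05. The next sentence, which gives the DSMC a part in the discussion, says that "a decision will be made with respect to continuing recruitment based on both the statistical significance and clinical relevance of any effect observed".

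**The concern.** A power figure is useful when it refers to the test that will be applied. Here the only significance test defined for the interim is at .001, while the only operating characteristic given for it is calculated at 0.05, a level at which no interim action is defined. The 80% leads straight into a sentence that makes statistical significance one of two bases for deciding whether to go on recruiting.

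A committee that carries the 80% over to the .001 test would take a non-crossing as fairly strong evidence against a 30% effect. In fact non-crossing is the expected result when the vaccine works exactly as planned. A second, smaller question is whether 80% is right even at 0.05.

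**Working it through.** **Inputs.** Control rate 2.1, vaccine rate 1.47 (ratio 0.70), Poisson counts, one year per child, 1:1 allocation, two-sided tests: Sample size section and trial design. At the interim, 63 per group: Efficacy subsection. Critical values: 1.960 at 0.05, 3.291 at .001, 1.963 at .0497.

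**1. Reproducing the stated 80%.** The Signorini formula for Poisson regression gives

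N = [1.960·√4 + 0.842·√(2 + 2/0.70)]² / (2.1·(ln 0.70)²) = 33.35 / 0.2672 = 124.8,

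that is 63 per group. Power with 126 children is Φ[(√(126·2.1)·0.3567 − 1.960·2) / 2.204] = Φ(0.854) = 80.3%. The stated figure is reproduced.

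**2. Direct comparison of the two rates at 0.05.**

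- Difference: SE = √((2.1 + 1.47)/63) = 0.2380; 0.63/0.2380 = 2.647; power = Φ(2.647 − 1.960) = 75.4%.
- Log rate ratio: SE = √((1/2.1 + 1/1.47)/63) = 0.1355; 0.3567/0.1355 = 2.633; power = Φ(2.633 − 1.960) = 74.9%.
- Exact conditional binomial test: 73.5%. Simulated Poisson trials: about 75% to 76%.
- Size needed for 80% on the difference scale: (1.960 + 0.842)²·3.57/0.63² = 70.6. The direct methods together give 70 to 72 per group.

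**3. Consistency with the Sample size section.** Power of 90% at 93 per group implies a standardised effect of 1.960 + 1.282 = 3.242. At 63 per group this is 3.242·√(63/93) = 2.668, and Φ(2.668 − 1.960) = 76%. In the other direction, 80% at 63 implies Φ(2.802·√(93/63) − 1.960) = 92.6% at 93, not 90%.

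**4. Power at the boundary that will be used (.001).**

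| Basis | Calculation | Power |
|---|---|---|
| Difference | Φ(2.647 − 3.291) | 26.0% |
| Log rate ratio | Φ(2.633 − 3.291) | 25.5% |
| Exact conditional | enumeration | 24% |
| Simulation | Poisson trials | 25% to 26% |
| Stated 80% accepted | Φ(0.842 + 1.960 − 3.291) | 31% |
| Signorini | Φ[(5.802 − 3.291·2)/2.204] | 36% |

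At a control rate of 2.1, the observed reduction must be about 37% to cross. A 37% reduction gives 0.777/√(3.423/63) = 3.33, and 36% gives 0.756/√(3.444/63) = 3.23, against 3.291.

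**5. What a non-crossing means under the design effect.** The interim and final statistics are taken as jointly normal with correlation √(63/93) = 0.823 and means 2.647 and 3.215 (difference scale). The chance of not crossing .001 is 74%. Given that, the chance of significance at .0497 with 93 per group is about 86%. The log scale gives 74% and 85%.

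**The case against.** The strongest reply is that nothing here is contradictory. The 80% carries its α openly, the .001 boundary stands in the same paragraph, and the article nowhere claims 80% power to cross it. A strict early boundary is meant to have low crossing power, and .001 with .0497 gives an overall two-sided α of about 0.0498. All of that stands. It clears the boundary of criticism, but it leaves the interim look described by a figure for a different test.

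A reader might infer that 80% is an arithmetic error. The documents do not support that: a published formula returns exactly 63 per group. It also gives 79.3% for the second full-trial statement (25% reduction, 93 per group, stated 80%) and 92.2% for the first (stated 90%). The direct difference method gives 75.2% and 89.5% for the same two. None of the formulas tried matches all three stated powers within 2 points. What remains is that the formula is optimistic here, because it puts the control rate in both arms under the null and simulation does not bear it out.

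The pilot SD of 1.046 in a two-means test would give 92% at 0.05 and 54% at .001. But the section says Poisson is assumed, and that SD would need only 58 per group for 90% power, not 93.

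A reader might also infer that the committee will misread the interim, or that a halt would destroy the final power. Neither follows. The α is labelled, clinical relevance counts as well as significance, and the text speaks of continuing recruitment, not of ending follow-up. The last of the 126 completers will have enrolled about 14 months before the look, so others may be enrolled by then. The accrual rate is not given, so the loss from a halt cannot be sized. The lack of a futility rule is something an article may leave to the full protocol or the DSMC charter, and is no part of this point.

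**Conclusion.** The point holds in a limited form. The interim look is justified by power at a level that will not be used. At .001 the power for a 30% reduction is about 26%, with 24% to 36% across Poisson formulas and 31% on the plan's own 80%. On every one of these figures, a non-crossing is more likely than not under the design effect. The 80% at 0.05 is formula-dependent and about 5 points optimistic, and it does not fit the 93 per group for 90% in the Sample size section.

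These figures assume Poisson variation, the planned rates, one full year per child and 63 completers in each group. The 85% to 86% chance of later success assumes that the trial goes on to 93 analysed per group. This is a correction to how the look is described. It shows no flaw in the boundary or the sample size.

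**What to change.** Replace the interim power sentence with: *63 per group give about 26% power to cross the .001 boundary for a 30% reduction (about 75% at an unadjusted two-sided 0.05).*

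Add: *Not crossing .001 is not by itself evidence against a 30% effect, nor a ground to stop recruitment. Under that effect about 75% of looks would not cross, and about 85% of those trials would be significant at the final .0497 level if completed.*

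If the sponsor prefers to keep the 80%, name the formula behind it and give the power at .001 beside it. The same wording should go to the DSMC before the interim look. The cost is one paragraph; no further children are needed, and the .001 and .0497 levels and the target of 206 stay as they are.

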#### Toxicity

During the trial, the occurrence of local or systemic reactogenicity may occur at rates that justify additional safety evaluations. If the conditions of any of the stopping rules are satisfied, the data will be assessed fully by the DSMC to determine that it is safe to continue the study. A multi-stage early stopping design approach [45] will be employed to define stopping rules after the occurrence of each observed SAE by comparing the total number of patients included to the maximal number of patients that satisfies maximal acceptable SAE criteria.

### Ethics approval

Human Research Ethics Committees of all the participating institutions have approved the study. It is being conducted under Australia’s Therapeutic Goods Administration Clinical Trial Notification scheme. The University of Queensland is the trial sponsor.

## Discussion

PBB, CSLD and bronchiectasis are important chronic paediatric respiratory illnesses globally. Repeated respiratory exacerbations in those with bronchiectasis are associated with significant long-term morbidity [25,46,47]. There is also historical precedent in the pre-antibiotic era that children with recurrent or persistent wet cough progressed from having normal radiographic appearance to those consistent with bronchiectasis [5]. As *H. influenzae* is the most common bacterial pathogen associated with these diseases in adults and children [18,19], a vaccine that could reduce or eliminate *H. influenzae* may avert exacerbations and reduce antibiotic use. This would be an important adjunct to current clinical management and may lead to short- and long-term health benefits. Our study, therefore, has clinical efficacy as the primary outcome and will be the first to assess the clinical impact of vaccines targeting *H. influenzae* in children with these diseases.

The systemic and mucosal immune responses, particularly antibody functionality, to PHiD-CV in children with recurrent PBB, CSLD and bronchiectasis have not been examined previously. Our study will examine responses to not only PD, but related *H. influenzae* proteins (P4 and P6) that have been considered as vaccine candidates as well as assessing responses to *S. pneumoniae* vaccine and vaccine-related serotype specific antigens*.* A prospective study of serum antibody response to three different *H. influenzae* outer membrane proteins (including PD) during episodes of AOM in otitis-prone and non-otitis-prone children highlights the importance of measuring immune responses in addition to clinical endpoints [48]. It reported diminished IgG responses to these antigens in otitis-prone children compared to non-otitis-prone children at the time of, and following, an AOM episode. Increased susceptibility in otitis-prone children might be related to suboptimal circulating functional T-helper memory and reduced IgG responses to *H. influenzae* or *S. pneumoniae* after colonisation and AOM [49]. These data support ongoing evaluation of responses in children at high-risk of *H. influenzae* infection.

Immunological responses to pneumococcal vaccine antigens are important to evaluate because of recent data suggesting diminished immunogenicity in children who have had either multiple exposures to vaccine antigens [50], or increased density of *S. pneumoniae* nasopharyngeal carriage at the time of vaccination [51,52]. The clinical significance of these observations, however, remains uncertain. A recent study has examined *S. pneumoniae* isolates from bronchoalveolar lavage (BAL) cultures of children with chronic cough thought to be due to PPB [53]. The results suggested significant differences in serotype distribution between 7vPCV vaccinated and unvaccinated children, with immunised children less likely to have vaccine serotypes isolated from BAL cultures, but also more likely to have non-vaccine serotypes than unimmunised children [53]. These findings are consistent with our own observations where pneumococcal conjugate vaccines appear to have had little impact on the burden of lower respiratory tract disease in high-risk Indigenous Australian populations [54], in whom *S. pneumoniae* isolates from nasopharyngeal and BAL cultures are principally non-vaccine serotypes [38,55]. Whether these differences resulted from host responses or population-based changes in circulating serotypes is unknown; however, the study suggests that ongoing surveillance of *S. pneumoniae* in this patient population is required.

It cannot be assumed that existing VE data against *H. influenzae* nasopharyngeal carriage and clinical disease (primarily AOM) in healthy young infants for PHiD-CV, and its 11-valent prototype in POET, can be generalised to preventing acute respiratory exacerbations in the lower airways of older children with PBB, CSLD or bronchiectasis. While the bacterial pathogens invading the middle ear cavities and the lower respiratory tracts of these patients are similar, the bacterial clearance mechanisms and immunity induced following a parenterally administered vaccine may differ between the two anatomical sites. In addition, a recent small study identified significantly reduced natural antibody levels to PD in adult patients with COPD (without exacerbation at time of specimen collection) and secondary immunodeficiency disorders compared to healthy controls, and that natural antibody levels declined with age [56]. Suboptimal circulating functional T-helper memory and reduced IgG responses to *S. pneumoniae* or *H. influenzae* have also been identified in otitis-prone children [49]. These data potentially indicate deficient host responses to *H. influenzae* infection in people with disease and that boosting antibody responses with vaccines may be required. Similar data do not exist for children with chronic lung diseases and, therefore, we have commenced an add-on study to the current protocol to examine this issue.

With respect to differences between nasopharyngeal carriage and disease, the POET study demonstrated a reduction in AOM caused by *H. influenzae*, but not nasopharygeal carriage by this organism in healthy children up to two years of age [33]. However, that study is not comparable to ours given the different population and primary endpoints and, in addition, the vaccine used possessed a higher content of PD than the currently licensed 10-valent PHiD-CV. Furthermore, there remains the possibility of different strains and virulence factors operating between colonisation and disease states [34]. Data comparing these factors between nasopharyngeal and lower airway *H. influenzae* isolates in children with non-CF bronchiectasis or other chronic lung diseases are virtually non-existent. A small study conducted in Australian Indigenous children [38], a population with extensive *H. influenzae* acquisition very early in life [57] and excessive rates of recurrent upper and lower respiratory tract infections [58], found a high density and diversity of respiratory bacteria. It also found nasopharyngeal and BAL strain concordance between the upper and lower airways in 45 children with HRCT confirmed bronchiectasis. However, this study was not conducted at the time of an acute exacerbation and 27 (60%) had received antibiotics within two weeks of specimen collection [38].

Currently, data on PHiD-CV VE against *H. influenzae* carriage and disease in older children are limited to the results from a single study involving healthy four-year-olds [59]. This was a follow-up study of an earlier trial [60] of the PHiD-CV in Czech children conducted when they were 31 to 44 months of age. Persistence of NTHi nasopharyngeal carriage was a secondary objective. Thirty percent of the original cohort (n = 686) did not participate in the follow-up study. Children primed previously with PHiD-CV received a fifth dose at 40 to 48 months of age, the unprimed group received two doses of PHiD-CV two months apart. Post-booster nasopharyngeal carriage data at 24 to 27 months of age from the first study suggested a VE against NTHi carriage of 51.2% (95% CI 11.7, 73.9). However, carriage increased in vaccinees (from 8.5% to 33.5%) and controls (17.3% to 38.9%) at each time point thereafter and, at ages of 31 to 44 months and 40 to 48 months, there was no difference between the two groups [59]. Carriage data beyond those time points have not yet been published.

In addition, the long-term impact of the vaccine on carriage of other microbes is similarly limited. In the same extension study of Czech children, there was no difference between groups in *Staphylococcus aureus* and *M. catarrhalis* carriage over the same time period [59]. This provides an early, albeit insufficient, indication that the PHiD-CV has not altered the dynamics of carriage of these two organisms in healthy young children over time. Whether the same findings occur in children with chronic lung diseases is currently unknown, although we have the capacity to examine these effects in additional laboratory studies outside of the current protocol. Nonetheless, replacement of vaccine type pneumococci by non-vaccine type serotypes has been observed commonly in experimental and non-experimental studies of other pneumococcal conjugate vaccines and in some studies increased carriage of *S. aureus* and *H. influenzae* has also been reported [61,62].

The two study vaccines have well established safety profiles in young children. However, as they are being administered outside of licensed indications in Australia, and to a population of children with existing morbidities, we will undertake a complete safety evaluation during the trial. Our safety endpoints are consistent with those used in trials of both vaccines and SAE monitoring is consistent with Good Clinical Practice criteria [63].

In summary, our RCT will be the first to examine the impact of a vaccine targeting *H. influenzae* in children with recurrent PBB, CSLD and bronchiectasis. The best evidence to answer questions about strain concordance, acquisition of new strains and subsequent infection in the lower airways, and changes in the microbiological profile of acute exacerbations in children with chronic lung diseases following vaccination with PHiD-CV, are best obtained if BALs are performed at baseline, at each study time point and during acute exacerbations. This is ethically unacceptable and, hence, our choice of a clinical endpoint as the primary objective follows the concept of vaccine probe studies as markers of disease burden [64], as demonstrated previously in pneumococcal conjugate and Hib vaccine trials. Clinical efficacy will be evaluated in the context of detailed nasopharyngeal carriage, immunogenicity, lung function and safety data to provide a detailed assessment of whether vaccines may reduce exacerbations and provide an opportunity to improve long-term health outcomes. The study will also be an important contribution to the literature on the effects of conjugate vaccines on the nasopharyngeal microbiology of children with recurrent PBB, CSLD and bronchiectasis.

## Trial status

Recruitment began in January 2013.

## Abbreviations

7vPCV: 7-valent pneumococcal conjugate vaccine; AOM: Acute otitis media; BAL: Bronchoalveolar lavage; CF: Cystic fibrosis; cHRCT: Chest high-resolution computed tomography; CI: Confidence intervals; COPD: Chronic obstructive pulmonary disease; CSLD: Chronic suppurative lung disease; DSMC: Data Safety Monitoring Committee; NTHi: Non-typeable *Haemophilus influenzae*; PBB: Protracted bacterial bronchitis; PBS: Phosphated buffered saline; PCR: Polymerase chain reaction; PD: Protein D; PHiD-CV: Pneumococcal-*Haemophilus influenzae* protein D conjugate vaccine; POET study: Pneumococcal Otitis Efficacy Trial; QoL: Quality of life; RCT: Randomised controlled trial; RR: Relative risk; SAE: Serious adverse event; VE: Vaccine efficacy; WHO: World Health Organization.
